#### **5.6.5.10    Disseminated Intravascular Coagulation**

If either aPTT  $\geq 1.5 \times$  ULN, or thrombocytes  $< 75 \times 10^9$ /L or fibrinogen  $< 50\%$  of LLN are reached, the tests for fibrin split products and D-dimer should be performed. If fibrin split products and/or D-dimers are  $> \text{ULN}$ , and the aPTT or thrombocytes or fibrinogen remain outside of protocol limits as described above, study drug must be stopped and the subject should be immediately withdrawn from the study if not already discontinued. An elevated d-dimer or fibrin split products in the absence of aPTT  $> 1.5 \times$  ULN, or thrombocytes  $< 75 \times 10^9$ /L or fibrinogen  $< 50\%$  of LLN does not require stopping study drug unless it is associated with clinical signs or symptoms (e.g. bleeding).

### **5.6.6      Adverse events**

The investigator will determine whether any AEs have occurred between visits. The subjects will be questioned using non leading questions and no specific symptoms will be suggested. Refer to section 7 for further information on adverse event reporting.

### **5.6.7 Concomitant medication**

The investigator should record the use of all concomitant medications, both prescribed and over-the-counter, on the CRF. This includes drugs used on a chronic and as-needed basis. The following will be recorded on the CRF: name of medication, reason for taking concomitant medication, dose, unit, regimen, route of administration, start date and end date (if applicable).

### **5.6.8 Laboratory Safety Parameter Stopping and Follow-up Criteria**

#### **5.6.8.1 Hepatic Toxicity**

Laboratory safety assessments including liver chemistries will be performed at selected visits, refer to Tables 6 - 14 in Appendix 2 for exact time points.

- ALAT  $\geq 8x$  ULN and total bilirubin  $2x$  ULN (plus  $>35\%$  'direct' bilirubin) or ALAT  $\geq 8x$  ULN and INR  $>1.5$ .
- $\gamma$ -GT  $>2x$  ULN and bilirubin  $2x$  ULN (plus  $>35\%$  'direct' bilirubin) or  $\gamma$ -GT  $>2x$  ULN and INR  $>1.5$

If a subject's results meet either of these criteria, the tests should be repeated immediately. If the results still meet these criteria, the study medication should be stopped until such time that the Sponsor (in discussion with the Investigator) considers that the benefit of further treatment with PRO051 outweighs the risk to the individual subject.

NOTE: if serum bilirubin fractionation is not immediately available, study medication should be discontinued if ALAT  $\geq 8x$  ULN and total bilirubin  $\geq 2x$  ULN. Serum bilirubin fractionation should be performed if testing is available. If testing is unavailable, record presence of detectable urinary bilirubin on dipstick, indicating direct bilirubin elevations and suggesting liver injury.

- ALAT  $\geq 8x$  ULN associated with symptoms of hepatitis (e.g. onset or worsening of nausea, anorexia, jaundice or abdominal pain) or hypersensitivity (fever, rash, eosinophilia).

If a subject's results meet this criterion, the test should be repeated immediately alongside a discussion with the Medical Monitor. Depending on the result of the re-test and general clinical picture, appropriate action with regards to discontinuing study medication will be decided between the Sponsor and Investigator.

Given the progressive and fatal nature of this disease, it is felt important that the hepatic stopping criteria allow the flexibility for the potential to re-start dosing in this subject population following an individual subject benefit: risk assessment.

However, if a subject's results meet the criterion below, the tests should be repeated immediately. If the results still meet this criterion, the study drug should be permanently stopped.

ALT  $>2x$  baseline values and bilirubin  $2x$  ULN (plus  $>35\%$  'direct' bilirubin) or ALT  $>2x$  baseline values and INR  $>1.5$ .

Standard liver follow-up will be implemented following repeat testing confirmation of any of liver findings as described above. If a subject's results meet any of these criteria the following processes should be completed:

- Report the event to Prosensa within 24 hours of learning of its occurrence;

- Complete the appropriate case report form (CRF) and SAE data collection tool. Note: all events mentioned above must be reported as an SAE.;
- Complete the liver imaging and/or liver biopsy CRFs if these tests are performed;
- Make every reasonable attempt to have subjects return to clinic within 24 hours for repeat liver chemistries, liver event follow up assessments (see below), and close monitoring;
- A specialist or hepatology consultation is recommended;
- Monitor subjects twice weekly until liver chemistries (ALAT, ASAT, alkaline phosphatase, bilirubin) resolve, stabilize or return to within baseline values.

In addition, make every attempt to carry out the liver event follow up assessments described below:

- Viral hepatitis serology including:
  - Hepatitis A immunoglobulin M (IgM) antibody;
  - Hepatitis B surface antigen and Hepatitis B Core Antibody (IgM);
  - Hepatitis C RNA;
  - Cytomegalovirus IgM antibody;
  - Epstein-Barr viral capsid antigen IgM antibody (or if unavailable, obtain heterophile antibody or monospot testing);
  - Hepatitis E IgM antibody;
- Serum creatine kinase (CK), glutamate dehydrogenase (GLDH) and lactate dehydrogenase (LDH);
- Fractionate bilirubin, if total bilirubin  $\geq 2x$  ULN;
- Obtain complete blood count with differential to assess eosinophilia;
- Collect blood sample for measurement of drug concentration within one month of last dose. Record the date/time of this blood sample draw and the date/time of the last dose of study medication prior to blood sample draw on the CRF. If the date/time of the last dose is unclear, provide the subject's best approximation. If the date/time of the last dose cannot be approximated OR a PK sample cannot be collected in the time period indicated above, do not obtain a PK sample. Instructions for sample handling and shipping are provided in the SPM;
- Record the appearance or worsening of clinical symptoms of hepatitis or hypersensitivity, such as fatigue, nausea, vomiting, right upper quadrant pain or tenderness, fever rash or eosinophilia as relevant on the AE report form;
- Record use of concomitant medications, acetaminophen (=paracetamol), herbal remedies, other over-the-counter medications, or putative hepatotoxins, on the concomitant medications report form;
- Record alcohol use on the liver event alcohol intake CRF.

The following are required for subjects with ALAT  $\geq 8x$  ULN and total bilirubin  $\geq 2x$  ULN ( $>35\%$  direct) but are optional for other abnormal liver chemistries:

- Anti-nuclear antibody, anti-smooth muscle antibody, and Type 1 anti-liver kidney microsomal antibodies;
- Liver imaging (ultrasound, magnetic resonance, or computerized tomography) to evaluate liver disease.

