### **5.3.4      Safety laboratory (routine biochemistry and hematology, coagulation, urinalysis, complement activation, inflammatory and immune response)**

#### **5.3.4.1      Routine biochemistry and hematology**

Routine biochemistry and hematology will be performed at visit 1, visit 1a, visit 2 prior to the first injection, visit 3, visit 4, visit 5, visit 6, visit 7, visit 9 and visit 12.

The parameters to be assessed for routine biochemistry and hematology are described in Appendix 3. There is no food restriction prior to blood sampling. The samples will be collected and processed according to standard hospital procedures and assessed by the local laboratory of the participating sites.

Special attention is required for the liver related enzymes in the clinical biochemistry assessments. A number of these liver enzymes (ASAT, ALAT and LDH) are also present in muscle and hence elevated levels are found in plasma (or serum) upon muscle damage, as in DMD patients. Indeed, these ASAT and ALAT findings in DMD patients have been found to correlate quantitatively with muscle specific CK levels in plasma (or serum) in DMD patients. Therefore, changes in ASAT and ALAT should be monitored in relation to CK for the evaluation of hepatotoxicity. If the changes in ASAT and ALAT levels (of over 3xULN) is disproportional to the CK changes, further evaluation is required. Dependent on the findings, this can include (i) further data analysis (e.g. graphical evaluation of trends in ALAT, ASAT and CK over time and compared to pre-treatment levels and/or regression analysis between ALAT/ASAT and CK levels for all samples of the patient), (ii) taking an additional confirmatory sample, (iii) starting more frequent monitoring and/or (iv) evaluating other alternative explanations. The sponsor should be notified of such concern. If deemed necessary, drug administration will be discontinued.

Other measures of hepatic and biliary function, including bilirubin,  $\gamma$ GT and ALP are not affected by the disease. However, ALP may be influenced by age (ALP from bone).

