### **5.6.5 Safety laboratory**

### **5.6.5.1      Routine biochemistry and hematology**

Routine biochemistry and hematology will be performed at selected visits, refer to Tables 6 - 14 in Appendix 2 for the exact time points.

The parameters to be assessed for routine biochemistry and hematology are described in Appendix 3. There is no food restriction prior to blood sampling. The samples will be collected and processed according to standard hospital procedures and assessed by the local laboratory of the participating sites.

Non-clinical studies with PRO051 suggest that it potentially may have hepatotoxic and nephrotoxic properties as it accumulates in the liver and kidney and is also associated with thrombocytopenia.

Therefore, monitoring of hepatic and renal function as well as thrombocyte count is of paramount importance. However, standard markers of hepatic and renal function may be confounded by the effects of DMD e.g. DMD subjects may have elevated ALAT, ASAT and CK levels (common markers of hepatic function) due to 'leaky' sarcolemmal membranes around muscle fibers, and serum and urinary creatinine concentrations (markers of renal function) may be variable due to changes in muscle mass. With this information in mind, the following parameters will be used for monitoring hepatic and renal function:

Hepatic function:      ALAT, ASAT, ALP, total bilirubin, bilirubin fractions (direct bilirubin),  $\gamma$ -GT, GLDH and LDH.

Renal function:      Urinalysis (including microscopy), serum and urine cystatin C, KIM-1, alpha-1-microglobulin and serum creatinine.

Urinalysis will be conducted on the first morning specimen after 8 hours of not drinking.

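### Section 5.6.8.1: while the direct-bilirubin fraction is delayed or untestable, only the ALAT ≥8x ULN criterion has a fallback stop; the gamma-GT and ALT >2x baseline criteria have no interim hold

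*Protocol*

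**What the plan says.** Protocol section 5.6.8.1 sets these laboratory criteria for the treatment beyond the study period:

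- ALAT ≥8x ULN, with either bilirubin 2x ULN of which more than 35% is direct, or INR >1.5. If a repeat confirms it, drug is stopped, with restart possible.
- Gamma-GT >2x ULN, with the same two arms and the same action.
- ALT >2x baseline, with the same two arms. Here "If the results still meet this criterion, the study drug should be permanently stopped".

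A further criterion, ALAT ≥8x ULN with symptoms, does not use bilirubin.

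The NOTE after the first two criteria deals with a missing fraction: "if serum bilirubin fractionation is not immediately available, study medication should be discontinued if ALAT" is at least 8x ULN and total bilirubin at least 2x ULN. It then asks for fractionation wherever the test is available. Where it is not, sites are to "record presence of detectable urinary bilirubin on dipstick, indicating direct bilirubin elevations and suggesting liver injury". No dosing action is tied to the dipstick result.

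On follow-up, the section says: "Standard liver follow-up will be implemented following repeat testing confirmation of any of liver findings as described above". One item in that follow-up is "Fractionate bilirubin, if total bilirubin" reaches 2x ULN. Section 5.6.5.1 lists direct bilirubin among the planned hepatic parameters; Appendix 3 lists bilirubin without fractions.

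**The concern.** The NOTE accepts that the fraction may be missing when a dosing decision is due, and it supplies a substitute rule for one of the three criteria that depend on it. For the other two, the bilirubin arm cannot be evaluated until the fraction arrives. A criterion that cannot be evaluated prompts neither a repeat test nor a stop, and it cannot start the confirmed-finding follow-up.

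The omission matters because of which criteria are left out. Section 5.3.4.1 explains that ASAT and ALAT are raised by muscle damage in this disease, and then says "Other measures of hepatic and biliary function, including bilirubin", gamma-GT and ALP are not affected by it. So the fallback covers the enzyme that the disease confounds and omits the one that it does not. The other omission is the only criterion that ends treatment permanently. Section 5.6.5.1 treats hepatic monitoring as essential because the drug accumulates in the liver.

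**Working it through.** No sample size or error rate is involved. The check has three parts. The criteria print bilirubin as 2x ULN without an inequality sign; it is read here as at least 2x, as in the NOTE. ALT and ALAT are the same enzyme.

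**1. Each criterion with the fraction unknown.** Assume total bilirubin ≥2x ULN and INR ≤1.5, so that the INR arms are not met.

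| Finding | Stated action in 5.6.8.1 while the fraction is unknown |
|---|---|
| ALAT ≥8x ULN | Discontinue (NOTE) |
| Gamma-GT >2x ULN, ALAT <8x ULN | No stop, no repeat-test trigger |
| ALT >2x baseline, ALT <8x ULN | No stop, no repeat-test trigger |

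If INR exceeds 1.5, all three criteria can be read without the fraction.

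**2. When the ALT gap exists.** Write baseline ALT as b x ULN. The permanent criterion begins above 2b x ULN and the NOTE's fallback begins at 8x ULN. The uncovered range runs from 2b to 8, and is non-empty only if 2b < 8, that is b < 4. The protocol gives no baseline ALT, so b is an assumption:

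- b = 1: ALT between 2x and 8x ULN is uncovered.
- b = 2: between 4x and 8x ULN.
- b = 3: between 6x and 8x ULN.
- b ≥ 4: nothing is uncovered, because any ALT above 2x baseline also exceeds 8x ULN. The NOTE then stops drug, although under the restartable ALAT criterion.

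The gamma-GT gap does not depend on b.

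**3. Worst-case exposure.** Suppose the criterion stays unread until the next scheduled safety biochemistry. Draws precede dosing on the same day (footnote 1 of the tables), so only doses on later days are counted.

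Eight weeks on, four weeks off (Appendix 2, Tables 9 and 10). Dosing visits are 94–101, 106–113, 118–125 and 130–133.

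- 93 to 97: doses at 94, 95, 96 = 3
- 97 to 101: 98, 99, 100 = 3
- 101 to 106: off-drug break = 0
- 106 to 109: 107, 108 = 2
- 118 to 121: 119, 120 = 2
- 121 to 125: 122, 123, 124 = 3
- 125 to 130: off-drug break = 0

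The range is 0 to 3 doses. Section 3.3 sets the dose at 6 mg/kg up to 50 kg and 300 mg above that, so the maximum is 3 × 6 = 18 mg/kg, or 3 × 300 = 900 mg.

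Weekly dosing option (Table 12), with draws at 161, 166, 169, 173, 178 and 181: the intervals contain 4, 2, 3, 4 and 2 later-day doses. The maximum is 4 × 6 = 24 mg/kg, or 4 × 300 = 1200 mg.

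**The case against.** The strongest reply is that the NOTE itself orders fractionation wherever the test can be done. That instruction is not limited to ALAT ≥8x ULN and does not wait for a confirmed criterion. Direct bilirubin is also a planned parameter in section 5.6.5.1. Where testing is possible, the missing information should therefore arrive, and a delay shorter than the seven-day dosing interval need not change any dose. This stands, and it sets the limits of the point: what remains is the wait for a delayed result, and the site that cannot test at all, where the dipstick is only recorded.

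Second, requiring the fraction before an irreversible stop is defensible in a progressive, fatal disease. The section says "it is felt important that the hepatic stopping criteria allow the flexibility for the potential to re-start dosing". This is a good argument against making an unconfirmed stop permanent. It does not argue against a temporary hold, which the protocol already accepts for the ALAT criterion.

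Third, the protocol describes ALAT as raised in this disease. If baselines are commonly 4x ULN or higher, the ALT half of the gap disappears. That is possible but cannot be checked from the document, and it leaves the gamma-GT half untouched.

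Fourth, other safeguards exist: withdrawal at the investigator's judgement (4.5), the investigator's assessment of laboratory changes (7.2.1.2) and monthly internal safety board review (8.3). They reduce the risk, but none is a stated hold for these two criteria.

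**Conclusion.** The gap is real, narrow and minor. While the fraction is delayed or untestable, INR is ≤1.5 and ALAT is below 8x ULN, section 5.6.8.1 states no stop and no repeat test for bilirubin ≥2x ULN with gamma-GT >2x ULN. The same holds for ALT >2x baseline, on the assumption that baseline ALT is below 4x ULN. The gamma-GT part is the firmer of the two.

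A reader might infer three stronger things that the protocol does not support:

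- That nothing obtains the fraction until a criterion has been confirmed. The follow-up list does work that way, but the NOTE separately orders the test where it is available.
- That two or three further doses always follow. After the last on-drug draw of a cycle the number is 0. The 0 to 3 doses, or up to 4 under weekly dosing, are what could fall due if the criterion stayed unread until the next draw; they do not predict exposure.
- That a known share of boys is exposed to undetected liver injury. The protocol allows no frequency to be derived, and the INR arms and investigator discretion remain in force.

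**What to change.** Extend the NOTE in section 5.6.8.1 along these lines: when the fraction is not immediately available, also withhold study drug if total bilirubin is ≥2x ULN together with gamma-GT >2x ULN or with ALT >2x baseline.

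Give the hold an end. It lasts until the fraction is obtained and the criterion can be read. Where fractionation cannot be done at all, it lasts until the sponsor and investigator decide on restart by individual benefit:risk assessment, using the repeat liver tests and the urine bilirubin dipstick. The stop becomes permanent only if the ALT >2x baseline criterion is then confirmed.

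This needs a short addition to the NOTE and no new test, since section 5.6.5.1 already lists direct bilirubin. It also gives the dipstick result a use and keeps restart possible. The cost is an occasional temporary hold that proves unnecessary.

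### Protocol 5.6.8.1 lets gamma-GT and INR trigger a liver event but ends twice-weekly monitoring on four other tests, so after a gamma-GT plus INR event it can end with both triggers still abnormal

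*Protocol*

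**What the plan says.** Protocol 5.6.8.1 builds its hepatic criteria from ALAT (written ALT in the last one), gamma-GT, bilirubin with its direct fraction, INR and symptoms. For the first two criteria, one led by ALAT and one by gamma-GT, "If a subject's results meet either of these criteria, the tests should be repeated immediately". If confirmed, drug is stopped until the sponsor, in discussion with the investigator, judges that benefit outweighs risk. A further ALAT criterion with symptoms leads to a repeat test and a joint decision. The last criterion, on a rise from baseline, leads to a permanent stop.

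The same section then sets the scope of the follow-up: "Standard liver follow-up will be implemented following repeat testing confirmation of any of liver findings as described above". That covers every criterion, including those led by gamma-GT or completed by INR. The duration of the close monitoring is given as: "Monitor subjects twice weekly until liver chemistries (ALAT, ASAT, alkaline phosphatase, bilirubin) resolve, stabilize or return to within baseline values".

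The liver event assessments that follow name viral serology, "Serum creatine kinase (CK), glutamate dehydrogenase (GLDH) and lactate dehydrogenase (LDH"), bilirubin fractionation, a blood count, a drug concentration sample, autoantibodies and imaging. Neither gamma-GT nor INR is among them.

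Elsewhere, 5.6.5.1 defines the tests for monitoring hepatic function in the extension. That panel opens with "ALAT, ASAT, ALP, total bilirubin, bilirubin fractions (direct bilirubin") and continues with gamma-GT, GLDH and LDH.

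**The concern.** A rule that ends monitoring should look at the tests that started it. Here the trigger list and the end list sit in one section and do not match. Followed as written, the rule can be satisfied by tests that played no part in the event.

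The choice of tests also sits awkwardly with the protocol's own reasoning. Section 5.6.5.1 warns that ALAT and ASAT may be raised by the muscle disease itself, and both are on the end list. Section 5.3.4.1 says that bilirubin, gamma-GT "and ALP are not affected by the disease" (with a caution that ALP may vary with age). Of those three, gamma-GT is the one left off.

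At stake is the record of how a confirmed liver signal evolved in a child off drug. These events are all reportable as serious. The sponsor and investigator then weigh benefit against risk for most of them. The course of the triggering test is the natural evidence for that judgement, and the protocol does not require it to be collected at the twice-weekly checks.

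**Working it through.** The plan states no figure here, so the check is a comparison of lists.

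**Inputs.** The criteria, the scope of follow-up and the end-of-monitoring list are all from 5.6.8.1. The hepatic panel is from 5.6.5.1. The routine schedule is from Appendix 2, Tables 6 to 14, with test contents from Appendix 3.

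**Step 1: set each trigger against the end list (ALAT, ASAT, ALP, bilirubin).**

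| Limb | Trigger | On the end list | Not on the end list |
|---|---|---|---|
| 1 | ALAT at least 8 x ULN + bilirubin | ALAT, bilirubin | none |
| 2 | ALAT at least 8 x ULN + INR > 1.5 | ALAT | INR |
| 3 | gamma-GT > 2 x ULN + bilirubin | bilirubin | gamma-GT |
| 4 | gamma-GT > 2 x ULN + INR > 1.5 | none | gamma-GT, INR |
| 5 | ALAT at least 8 x ULN + symptoms | ALAT | none |
| 6 | ALT > 2 x baseline + bilirubin | ALAT (ALT), bilirubin | none |
| 7 | ALT > 2 x baseline + INR > 1.5 | ALAT (ALT) | INR |

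**Step 2: count.** Limbs: 3 led by ALAT at least 8 x ULN, plus 2 led by gamma-GT, plus 2 led by ALT above 2 x baseline, makes 7. Limbs with at least one trigger off the list: 2, 3, 4 and 7, so 4 of 7. Limbs with every trigger off the list: limb 4 only, so 1 of 7. The remaining 4 - 1 = 3 keep one trigger under observation.

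**Step 3: apply the rule to limb 4.** Suppose gamma-GT and INR are confirmed abnormal, bilirubin and ALP are at baseline, and ALAT and ASAT are at the boy's usual muscle-derived level. All four listed tests are already within baseline, so the end condition holds at the first check, whatever gamma-GT and INR show.

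**Step 4: look for another provision that closes the gap.**
- The return visit within 24 hours asks for repeat liver chemistries without defining them. Read broadly this may include gamma-GT, which Appendix 3 lists under biochemistry. It would not naturally include INR, which Appendix 3 lists under coagulation.
- Gamma-GT is part of routine biochemistry, and INR is scheduled from Table 8 on (Tables 6 and 7 list aPTT only). In Table 10 both fall at visits 113, 118, 121, 125, 130 and 133. The intervals are 5, 3, 4, 5 and 3 weeks: 20 weeks over 5 intervals, or 4 weeks on average. A four-week interval would otherwise hold 4 x 2 = 8 twice-weekly checks.
- Tables 10 to 14 require no laboratory visit in the treatment break unless there is a medical or safety concern.
- Section 7.3 requires follow-up reports on a serious event until it resolves or stabilises, but names no tests.

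None of these requires gamma-GT and INR at the twice-weekly checks.

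**The case against.** The sentence at issue fixes only how long the extra twice-weekly monitoring lasts, and it also accepts stabilisation. A reader might infer three stronger things that the protocol does not support.

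- *That the boy is declared resolved or the event is closed.* Section 7.3 governs follow-up of serious events and does not refer to the four tests. Section 7.4 adds re-evaluation of possibly or probably related events still present when the subject completes or is withdrawn.
- *That drug can be restarted on the four tests.* Restart is a separate benefit-risk decision under 5.6.8.1 and 6.4. For the two limbs based on a rise from baseline the stop is permanent, so there is no restart to misinform.
- *That gamma-GT and INR go unmeasured.* Both are repeated at confirmation and, from Table 8 on, both are on the routine schedule. The accurate statement is that the liver follow-up does not require them. Investigators may order more, and specialist consultation is recommended.

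The size can also be challenged. In three of the four affected limbs a trigger test is still followed, and monitoring continues while it remains abnormal and unstable. The full consequence needs limb 4, with the four listed tests quiet while INR exceeds 1.5, and the documents do not show how often that would occur. Nor is the list blind to muscle confounding: two of the three tests that 5.3.4.1 calls unaffected by the disease are on it, and CK, GLDH and LDH are among the assessments.

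All of this stands and limits the consequence. It does not remove the mismatch. The follow-up expressly applies to every confirmed finding, the end list omits two of the triggers, and no other provision supplies them during that follow-up.

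**Conclusion.** Section 5.6.8.1 is internally inconsistent. Four of its seven trigger limbs use a test absent from the end-of-monitoring list. In three of them one trigger is still watched, so monitoring could end with the other trigger unsettled. In one, gamma-GT above 2 x ULN with INR above 1.5, neither is watched. Twice-weekly monitoring can then end at the first check with both triggers abnormal and not required again until the next scheduled draw, three to five weeks apart in Table 10.

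This rests on reading the bracketed list as complete (it carries no wording to mark it as examples), on taking ALT and ALAT as the same test, and on routine visits continuing while drug is held. How often limb 4 would occur is unknown; it is presumably rare in a trial of 12 to 18 boys.

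The defect is a gap in safety follow-up data. It touches no analysis, sample size, dose-escalation decision or stopping threshold. It is still worth correcting, because the rule misfires when followed exactly and the repair is small.

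**What to change.** The sponsor should reconcile three texts: the end-of-monitoring list in 5.6.8.1, the criteria in the same section, and the hepatic panel in 5.6.5.1, so that the end of monitoring refers to the tests that triggered the event. It would help to define, in the same edit, what repeat liver chemistries covers at the 24-hour return visit. Which tests are followed, how often and to what level is a clinical choice that stays with the sponsor. No threshold or restart provision is in question here.

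The cost is a short edit to one section. If INR is among the tests followed, it may need a small coagulation sample of its own, since Appendix 3 lists coagulation apart from biochemistry and 5.6.5.7 draws a blood sample for aPTT. That volume should be checked against the limits in 3.3.
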